### 14.3 Assessment of Compliance

not applicable

### 14.4 Precautionary Measures

The following measures are listed in the respective SmPCs:

Severely dehydrated patients should receive intravenous electrolyte solutions first. Volume overload due to overdose should always be avoided. The dosage should be adjusted carefully. Severe haemodilution resulting from high doses of HES solutions should also be avoided in the treatment of hypovolaemic patients. (See section 11 for trigger of administration of blood products.) Elderly patients, who are more likely to suffer from cardiac insufficiency and renal impairment, should be closely monitored during treatment, and the dosage should be carefully adjusted, in order to avoid cardiocirculatory and renal complications resulting from hypervolaemia.

Further precautions as mentioned in the SmPc will not be mentioned in this section of the study protocol as respective patients are not to be included in the study: REFER TO SECTION 9.3 FOR CRITERIA OF PATIENTS WHO ARE *NOT ELIGIBLE* FOR PARTICIPATING IN THE PRESENT STUDY!

Because of the risk of allergic (anaphylactoid) reactions, the patient should be monitored closely.

Transiently raised alpha-amylase levels can occur after administration of solutions with HES. This should not be interpreted as a sign of pancreatic injury.

Because of the presence of calcium care should be taken to prevent extravasation during intravenous infusion. The solution should be given cautiously to patients with diseases associated with elevated vitamin D concentrations such as sarcoidosis. In case of concomitant blood transfusion, the solution must not be administered via the same infusion set. Solutions containing metabolisable anions should be administered cautiously to patients with respiratory impairment.

## **15 DURATION OF STUDY AND STUDY SCHEDULE**

### **15.1 Duration of study per patient**

Start of study: with randomisation

Treatment period (infusion of Investigational Products):

During surgery (guided by oesophageal Doppler measurements)

End of study: Postoperative day 15 or hospital discharge, whatever occurs first

Last evaluation of certain parameters will be 3 months post-surgery respectively when DRG data are available.

### **15.2 Study Schedule: Duration of whole study**

Planned start: June 2010

Planned recruitment time: 2 years

Planned last patient out: May 2012

## **16 STATISTICS**

### **16.1 Statistical methods**

This section gives an overview of the statistics planned for the study. All programming of tables, figures, listings and statistical analyses will be performed using the statistical software packages SPSS® version 13, SAS® version 9.1.3 and StatXact® version 6.

A Statistical Analysis Plan (StAP) will be finalized before close of database. It includes all protocol amendments. In case a protocol amendment is passed after finalization of the StAP an amendment to the StAP is to be composed.

All target criteria (primary and secondary variables) will first be examined by exploratory data analysis and descriptively evaluated (Wernecke 1995). In this setting, the evaluation of structural homogeneity of the treatment groups will be performed for the purpose of quality assurance.

A multiple primary endpoint consisting of “amount of HES-solution in ml” (first primary variable) and “days until fully on oral (solid) diet” (second primary variable) is defined. The principle of ordered hypothesis will be used (Hothorn and Lehmacher, 1991)(Maurer et al., 1995) for testing the two primary efficacy parameters. If the first primary hypothesis will result in a statistically significant difference of the amount of the hyperoncotic HES-solution as compared with the amount of iso-oncotic HES-solution, the second primary variable will be analyzed using the same procedure (with an unchanged error of the 1st kind  $\alpha = 5\%$ ) as described for the first primary variable.

The two primary variables will be evaluated with a non-parametric statistical test (Mann-Whitney U-test, Hartung and Elpelt, 1993) taking into consideration small sample sizes and possible deviation from normal distribution. Stratification variables will be included in the primary analysis as covariates (in a nonparametric analysis of covariance cf. Bathke, Brunner 2003).

Secondary target variables will also be evaluated with nonparametric tests according to their scaling. Whereby, in case of a small random sample size or an unbalanced condition, exact tests will be used (Mehta, Patel, 1998).

Because the study extends over a longer time period and during this time multiple readings/measurements will be taken from the patients, it is necessary to analyze the progress of the primary target criterion and further clinical parameters over the entire study period. Therefore, a non-parametric multivariate analysis of variance (MANOVA) (Brunner *et al.* 2002) for repeated measurement will be performed.

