## 9.5 Randomisation, Blinding and Unblinding

Patients will be randomized to either treatment in a 1:1:1 ratio.

The list of treatment assignments considering the stratification for investigational centre and ASA-class (2 strata:  $ASA \leq 2$  and  $ASA = 3$ ) will be generated by an independent study statistician comprised of consecutive blocks with the order of assignments chosen at random (i.e.: random permuted block of size 3, 6 or 9). The list will be prepared prior to the initiation of the study and will remain with the statistician. Based on this list the statistician will issue sets of random envelopes for each participating hospital, i. e. for the hospital's pharmacies for allocation the patient to the respective treatment and for the Principal Investigators for emergency unblinding (see below). The sponsor will receive a complete set of random envelopes also for emergency situations.

Patients who are eligible for inclusion into the study shall receive an increasing sequential patient number (enrolment number) in accordance with the order of their inclusion in the study. A random number will be issued which includes centre number and strata (A for  $ASA \leq II$ , B for  $ASA = III$ ) and an increasing consecutive number (within the ASA-class stratum). Enrolment of patients will be recorded in the enrolment log (appendix 4: a for stratum A and b for stratum B) A randomization sheet (appendix 5) will be issued with patient's data essential for compilation of the appropriate Investigational Product (Patient ID number, name and birthday – either hand written or use of hospital ID-label –, random number, ASA-class, body weight) and forwarded to the pharmacy to compile the appropriate amount of the respective Investigational Product.

Blinding will be performed by the hospital's pharmacy. In order to maintain blinding the following procedure has to be followed: The maximal possible daily dose for the 6% HES solution is determining the amount of bottles to be compiled for all treatment groups. In the group with HES 10% a balanced crystalloid fluid will be administered (in blinded manner) when the maximum daily dose of HES is reached. Thus, it will be ensured that in all treatment groups are the same amount of bottles (depending on bodyweight).

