## 10.2 Posology and Method of Administration

### 10.2.1 Dosage

Administration of Investigational Test and Reference Products will be performed as an “add on” fluid administration to a continuous basal crystalloid infusion.

The continuous basal infusion of the crystalloid will be 4 ml/kg bodyweight/h. A balanced crystalloid will be used for basal infusion (Sterofundin ISO).

The “add on” fluid administration of the Investigational Products i. e. of either HES 10%, HES 6% or crystalloid in a blinded manner with boluses of 250 ml will individually be controlled by measuring stroke volume with oesophageal Doppler to achieve a target controlled preload optimum. A detailed algorithm (flow diagram) will provide basis for amount of volume replacement (see also appendix 6)

[figure not shown]

If during surgery an acute haemodynamic deterioration occurs, indicated by an increase in heart rate and a concomitant drop in arterial blood or central venous pressure (as it might occur due to a surgical cause of bleeding) then the re-evaluation

of the Doppler signal has to be performed earlier than after 15 minutes to prevent systemic hypoperfusion.

In case intra-operative volume requirements exceed the amount of bottles of Investigational Product supplied by the pharmacy in a blinded manner then open-label treatment with a balanced crystalloid solution (Sterofundin ISO) will be performed during surgery (also using oesophageal Doppler measurements for deciding on the administration of the fluids).

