## 16.2 Level of significance and power

All tests will be conducted with an error of 1st kind  $\alpha = 5\%$ , two-sided.

Tests of secondary variables will be carried out in the area of exploratory data analysis. Therefore, corresponding p-values are to be regarded as exploratory ones and no adjustments for multiple testing will be made.

Sample size calculations are to be performed with a power of 80%

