## 16.4 Sample Size

The first primary variable, i. e. amount of plasma volume replacement therapy (in addition to a basal electrolyte infusion), will serve to calculate sample size. It is assumed that 250ml difference between the two HES treatment arms is clinically relevant.

It is roughly calculated that 228 patients shall be included which is based on the following assumptions: 69 patients per group, supposing an effect size (difference of means/(common standard deviation) =  $\frac{1}{2} = 0.5$ , error of the 1st kind  $\alpha = 5\%$  (two-sided), Power = 80% and the nonparametric Mann-Whitney U-Test (Calculations with

nQuery Advisor, version 6.0). Taking the drop-out rate of 10% into consideration, a sample size of 76 patients per group will be needed.

However, at present no reliable information is available on the amount of plasma volume requirement in elective pancreatic surgery. Thus, an internal pilot phase including 60 patients (including drop-outs) will be performed in order to re-calculate total sample size. For re-calculation the pooled variance will be assessed on the grounds of clinical relevant difference without unblinding. Type I error for both phases of the study will strictly be maintained. (Kieser and Friede, 2000 and 2003)

For the second primary endpoint it is assumed that 1.5 day difference between the two treatment arms will be achieved. Based on hospital's own data an effect size (difference of means/ common standard deviation) of 0.698 is calculated which reveals that inclusion of 69 patients – as for the first primary endpoint (without dropouts) – will lead to a power of 97%. A sample size of only 37 (per group) is demanded to achieve a power of 80%. Therefore, enough power is ensured to prove the second primary endpoint after significance of the first. After pilot phase, the re-estimation of the (pooled) variance will also be accomplished for the second primary variable in order to ensure a sufficient power comparing the two treatments with the former re-calculated sample size (see above).

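### The protocol names only centre and ASA class as primary-analysis covariates; adding pre-operative body weight could gain precision on the millilitre endpoint that gates the second test

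*Protocol*

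**What the plan says.** Protocol 12.1 defines the first primary endpoint as the intraoperative amount of HES in ml, not scaled to body size. Under 16.1 the second endpoint (days until fully on oral diet) is tested only if the first is significant, and by the same procedure.

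On covariates, 16.1 states "Stratification variables will be included in the primary analysis as covariates", using a nonparametric analysis of covariance. Section 9.5 says the same and lists two stratification variables: ASA class (two strata) and centre. No other covariate is named in either place.

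Body weight is listed at the pre-operative visit in 14.1 and, under 9.5, goes on the randomisation sheet sent to the pharmacy. The synopsis visit list puts randomisation ahead of weight and 14.1 puts it after. Both belong to the same pre-operative visit, so weight is a pre-treatment value either way.

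Weight then determines supply. The number of bottles follows the per-kg maximum for HES 6%: "Thus, it will be ensured that in all treatment groups are the same amount of bottles (depending on bodyweight"). In the 9.5 example of a 70 kg patient, the ceiling is 3500 ml (7 bottles) for HES 6%. For HES 10% it is 2100 ml, rounded down to 4 bottles (2000 ml).

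**The concern.** The endpoint is an absolute volume, and its upper limit is proportional to body weight. If heavier patients receive more HES, the between-patient spread in weight stays in the error term of the gatekeeping test, although the variable that would remove it is on file for everyone and the planned method already accepts covariates.

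Planned power for this test is only 80%. Sections 9.4.1 and 16.7 stop the trial after the pilot phase if more than 228 patients would be needed, so lost precision cannot be bought back with a larger sample. A prognostic covariate is one of the few remaining ways to protect the test.

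**Working it through.** **Inputs from the protocol**
- Two-sided α of 5% and power of 80% (16.2).
- Section 16.4: "69 patients per group, supposing an effect size" of 0.5, for the Mann-Whitney test.
- Section 16.4: "It is assumed that 250ml difference between the two HES treatment arms is clinically relevant". With effect size 0.5 the implied SD is 250 / 0.5 = 500 ml.
- 10% drop-out, giving 76 per group and 3 × 76 = 228 in total (16.4).

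**Input not in the protocol**
- The correlation r between body weight and HES volume. Section 16.4 itself says that reliable information on volume requirement is lacking. I assume a range of 0 to 0.5.

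**Step 1: reproduce the plan's figure.** Noether's formula for the Mann-Whitney test, with p = Φ(d/√2), is

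N (two arms) = (z₀.₉₇₅ + z₀.₈₀)² / [3(p − 0.5)²].

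For d = 0.5, p = Φ(0.3536) = 0.6382. Then N = (1.960 + 0.842)² / [3 × 0.1382²] ≈ 137, or 68.5 per group. This rounds up to 69, as stated. Power at n = 69 is Φ(√(6 × 69) × 0.1382 − 1.960) = Φ(20.35 × 0.1382 − 1.960) = Φ(0.852), about 80.3%.

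**Step 2: add weight.** Removing the part of the variance explained by weight raises the effective effect size to d/√(1 − r²). For r = 0.3 this is 0.5/√0.91 = 0.524, so p = 0.6445 and power = Φ(20.35 × 0.1445 − 1.960) = Φ(0.981) = 83.7%.

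**Step 3: check by simulation.** I compared rank analysis of covariance on weight with the unadjusted Mann-Whitney test, using 69 per arm, 10,000 runs, normal data and the same weight slope in both arms.

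| r (assumed) | effective d | power at 69, formula | n per arm for 80% | simulated: Mann-Whitney | simulated: with weight |
|---|---|---|---|---|---|
| 0 | 0.500 | 80.3% | 69 | 81.3% | 80.9% |
| 0.1 | 0.503 | 80.6% | 68 | 80.8% | 81.1% |
| 0.2 | 0.510 | 81.8% | 66 | 80.8% | 82.4% |
| 0.3 | 0.524 | 83.7% | 63 | 81.7% | 84.3% |
| 0.4 | 0.546 | 86.3% | 59 | 81.6% | 87.0% |
| 0.5 | 0.577 | 89.7% | 53 | 81.3% | 89.6% |

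Simulated type I error stayed between 4.7% and 5.3% for both tests. At r = 0 the extra covariate cost 0.8126 − 0.8093 = 0.0033, about 0.3 points.

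**Limits of the calculation.** The comparator is an unadjusted test, whereas the plan already adjusts for centre and ASA class. The r that matters is therefore the partial correlation given those two factors. The formula also assumes a common weight slope. Where the ceilings bind, the slopes differ by design (50 against 30 ml/kg), so the figures are approximate.

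**The case against.** The strongest objection is that nothing in the plan is wrong. The test is valid, the sample size reproduces without weight, and 16.1 describes itself as an overview with a statistical analysis plan to follow. It says that the stratification variables will be included, not that no others may be. The first part stands: this is an efficiency point. The second carries less weight, because the protocol itself states the covariate set twice and names only those two factors. If the analysis plan adds weight before unblinding, the point is met.

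The second objection is that r could be small, and this stands. Study fluid is given in fixed 250 ml boluses titrated to stroke volume, not per kg. The ceilings matter only if reached. For the 70 kg patient that means 2000 / 250 = 8 boluses of HES 10% or 3500 / 250 = 14 of HES 6%, and the protocol does not say how often this is expected.

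A reader might also infer two stronger claims that the protocol does not support:
- **That the basal infusion makes weight drive the endpoint.** Section 10.2.1 says "The continuous basal infusion of the crystalloid will be 4 ml/kg bodyweight/h", but that fluid is crystalloid and lies outside an endpoint counted in ml of HES. Being scaled to weight, it may even absorb part of a weight effect.
- **That a chance imbalance in weight biases the test.** At 69 per arm, a 1.96-standard-error imbalance is 1.96 × √(2/69) = 0.33 SD of weight. At r = 0.3 that is 0.33 × 0.3 × 500 ≈ 50 ml, against the 250 ml target. Randomisation and the test's error rate already allow for such chance differences.

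**Conclusion.** The point holds as a recommendation to improve efficiency. The named covariates omit a baseline variable that is available for every patient and sets the ceiling of a millilitre endpoint. Adding it would raise power on the gatekeeping test from about 80% to roughly 82%, 84% or 86% if the partial correlation is 0.2, 0.3 or 0.4. It would cost about 0.3 points if the correlation is zero.

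These gains rest on an assumed correlation that nothing in the protocol pins down, on a common weight slope in the two HES arms, and on comparison with an unadjusted test. It would be a mistake to conclude that the primary test is invalid or that the trial falls short of its stated power: type I error holds and the 69 per group is correct without weight. Nor do the smaller sample sizes in the table justify enrolling fewer patients, since r is unknown.

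**What to change.** In 16.1, and in the matching sentence of 9.5:
- Name pre-operative body weight (the day −1 visit value, not the day +1 measurement) as an additional covariate, alongside centre and ASA class, in the nonparametric analysis of covariance for endpoint 1.
- State that carrying the same procedure over to endpoint 2 means adjusting for centre and ASA class only. Otherwise the present wording would take weight across as well.
- Report the weight-unadjusted analysis of endpoint 1 as a sensitivity analysis.

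Leave the sample size as it is. The cost is a few sentences, settled before unblinding, and one degree of freedom. No new data, method or change to treatment is needed.

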
\* if not otherwise mentioned measurements of secondary variables on ICU will be performed until fit-for-discharge from ICU criteria are fulfilled or until postoperative day 5 (including), whatever occurs first.

Efficacy:

- Haemodynamics
  - SAP, DAP, MAP, HR, CVP, CI, SV, SVR
  - cumulative dose of norepinephrine (mcg/h)
  - intrathoracic blood volume index (ITBVI) and extravascular lung water index (EVLWI), (PICCO)
- Time on ventilator (*measured from intubation in hours; the need of reintubation will be documented*)
- Requirements of postoperative ventilatory support (PCV, CPAP)
- Nursing Delirium Screening scale (NuDesc) – *measurement three times daily on ICU\**
- gastrointestinal parameters - (*measurement daily from post-op day +1 until fulfilment or until end of study, whatever occurs first*)
  - time until bowel movements (on auscultation)
  - time until full oral nutrition
  - time to first flatus
  - time to first defecation
  - intraabdominal pressure *measured baseline (after induction of anaesthesia), at the end of surgery (still in operating theatre before extubation), 6 hours after surgery, 1st post-operative day in the morning*
- SOFA, SAPS II, APACHE II Scores – *surveyed once daily on ICU\**
- length of stay in ICU/IMCU (fulfillment of ICU/IMCU release criteria according to the Aldrete Score, Aldrete 1995) *surveyed on admission to ICU, 1st postoperative day in the morning, at time of discharge from ICU*
- time until criteria for “fit for discharge from hospital” are fulfilled (hospitalization release criteria according to Marshall et al., 1999, Marshall and Chung, 1997) *surveyed once daily on ICU respectively surgical ward (if fit-for-discharge criteria are not fulfilled within the 5th postoperative day it will be controlled until fulfillment or until end of study, whatever occurs first)*
- Complication rate - surgical complications such as re-do surgery (e. g. anastomotic insufficiency or bowel leakage), disturbed wound-healing or medical complications which delay time to fully oral nutrition – *documentation at the study end*
- combined outcome parameter of prolonged length of stay (based on mean length of stay according to the German Diagnosis Related Group System D-DRG) or death (determination will be when DRG-data are available, i. e. after study end)
- Health Related Quality of Life (HRQoL) according to the EQ-5D questionnaire – *measurement baseline and 3 months after surgery*

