### Intraabdominal pressure

Measurements will be

- baseline (after induction of anaesthesia)
- at the end of surgery (still in operating theatre, directly before extubation)
- 6 hours after end of surgery
- 1st post-operative day in the morning

Technique:

Intraabdominal pressure will be obtained by measuring the intravesical pressure with the patient in a supine position. The bladder will be flushed via the transurethral catheter via a three-way stopcock using 25 mLs of sterile saline. The bladder will be emptied until air reaches three-way stopcock in order to exclude air bubbles in the system and to guarantee patency. As measurement volume 25 mLs sterile saline will be instilled. The manometer/pressure transducer will be connected to the transurethral catheter/connection to bladder via a three-way stopcock. Zero-reference will be at the midaxillary axis (same reference as CVP). Confirmation of correct measurement will be done by control of respiratory variation and the endexpiratory value will be noted.

In the awake patient (measurement at 6 hours after end of surgery and on 1st postoperative day in the morning) pain assessment will be made prior measurement of intraabdominal pressure using visual analogue scale (VAS).

Categories for pain assessment will be

|          |                      |
|----------|----------------------|
| VAS 0    | no pain              |
| VAS 1-3  | mild pain            |
| VAS 4-6  | medium/moderate pain |
| VAS 7-10 | intense pain         |

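### Section 16.1 specifies no baseline adjustment for secondary variables, although many of them have a pre-treatment value; adding it is a free, low-severity improvement

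*Protocol*

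**What the plan says.** Section 16.1 assigns methods by class of variable. The two primary variables get a Mann-Whitney test, and "Stratification variables will be included in the primary analysis as covariates" by a nonparametric analysis of covariance. Section 9.5 names those factors as centre and ASA class. The next paragraph covers the rest: "Secondary target variables will also be evaluated with nonparametric tests according to their scaling", with exact tests for small or unbalanced samples. No covariate is named there, and the tested quantity (follow-up value, change or adjusted value) is not stated.

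Section 16.1 then argues that "it is necessary to analyze the progress of the primary target criterion and further clinical parameters over the entire study period" and plans a nonparametric repeated-measures MANOVA. It does not say whether the baseline reading is a time level, a covariate or left out. The stated use of baseline data is checking that the groups are comparable (16.1 and the synopsis).

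On status, section 16.2 says "Tests of secondary variables will be carried out in the area of exploratory data analysis", without multiplicity adjustment. On further detail, 16.1 says "A Statistical Analysis Plan (StAP) will be finalized before close of database".

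**The concern.** Much of the secondary objective in section 7.2 rests on measurements taken both before and after study fluid: renal function, coagulation, haemodynamics, inflammation and intraabdominal pressure. If groups are compared on follow-up values alone, the spread that patients bring to the operating theatre stays in the error term. A real difference is then harder to see, and a chance imbalance at baseline can look like a treatment difference. Checking homogeneity may reveal such an imbalance but does not correct for it. No monitoring board is appointed (19.1.3), so the end-of-study comparisons carry much of the between-group safety evidence. The data for a sharper comparison are already being collected, and a suitable method is already cited for the primary variables.

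**Working it through.** **1. Which secondary variables have a pre-treatment value (sections 12.2, 12.3 and 14.1)**

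| With a baseline | Without a baseline |
|---|---|
| Pressures, heart rate, CI, SV, SVR, ITBVI, EVLWI | Norepinephrine dose, urine output |
| Blood gases, acid-base status, electrolytes | SIRS criteria, PONV, adverse events |
| Creatinine, BUN, urinary α1-MG and β-NAG | Blood products, blood loss |
| PT, aPTT, fibrinogen, vWF, FVIII, ROTEM | Ventilation time and support |
| Troponin, NT-pro-BNP | NuDesc, SOFA, SAPS II, APACHE II |
| PCT, CRP (IL6 and IL10 facultative) | Gastrointestinal times, Aldrete score |
| Intraabdominal pressure | ICU stay, time to fit for discharge |
| EQ-5D; calculated blood volume | Complications, prolonged stay or death |

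The day-0 baselines are taken after induction of anaesthesia and before the first bolus of study fluid (14.1). EQ-5D is taken before surgery. Both are therefore usable as covariates. In section 12.3 only haemodynamics, intraabdominal pressure and EQ-5D have a baseline.

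**2. Reproducing the protocol's own figures (section 16.4)**

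Inputs: two-sided 5%, power 80%, Mann-Whitney test, effect sizes 0.5 and 0.698.

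Noether's formula: n per group = (1.960 + 0.842)² / [6(p − 0.5)²], with p = Φ(d/√2).

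- d = 0.5: p = 0.6382; n = 7.849 / (6 × 0.1382²) = 68.5, so 69. Protocol: 69.
- d = 0.698: p = 0.6892; n = 7.849 / (6 × 0.1892²) = 36.5, so 37. Protocol: 37.
- Power at 69 per group for d = 0.698: 97.1%. Protocol: 97%.

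The formula matches, so it is used below.

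**3. Power with and without the baseline value**

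Assumptions that are not in the documents: a true difference of 0.4 SD, a baseline to follow-up correlation ρ between 0.3 and 0.7, and equal variance at both times. The documents supply 69 evaluable patients per arm.

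Power = Φ(√(6 × 69) × (p − 0.5) − 1.960).

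- Follow-up value only: p = Φ(0.4/√2) = 0.6114; 20.347 × 0.1114 = 2.266; power = Φ(0.306) = 62.0%.
- Baseline-adjusted: the SD shrinks by √(1 − ρ²), so d becomes 0.4/√(1 − ρ²).
- Change, or a two-point group-by-time contrast: d becomes 0.4/√(2(1 − ρ)).

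| ρ (assumed) | Residual variance, 1 − ρ² | Adjusted d | Follow-up only | Change contrast | Baseline-adjusted |
|---|---|---|---|---|---|
| 0.3 | 0.91 | 0.419 | 62.0% | 48.5% | 66.0% |
| 0.5 | 0.75 | 0.462 | 62.0% | 62.0% | 74.0% |
| 0.6 | 0.64 | 0.500 | 62.0% | 71.4% | 80.3% |
| 0.7 | 0.51 | 0.560 | 62.0% | 82.6% | 88.0% |

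The variance reduction is worth 1/(1 − ρ²) times the patients: 1.10, 1.33, 1.56 and 1.96 in the four rows.

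Adjustment has the highest power in every row. The change contrast falls below the follow-up-only test at ρ = 0.3, equals it at 0.5 and beats it above 0.5.

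The calculation treats the rank-based covariance method as having the efficiency of a Mann-Whitney test on residuals. It is an approximation.

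**The case against.** The strongest reply is that this belongs to the analysis plan. Section 16.1 describes itself as an overview and promises a separate plan, which is not shown. Covariates for exploratory comparisons are commonly settled there. This stands, and it caps the severity.

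A reader might infer from 16.1 that secondary variables are tested on follow-up values with baseline excluded. The text does not say so: it names a family of tests and neither includes nor rules out baseline. A reader might also infer that nearly all secondary variables have a baseline. The table in the working shows that they do not; ventilation, delirium and ICU scores, gastrointestinal times and event outcomes have none.

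The repeated-measures analysis also counts. If baseline enters as a time level, each patient's own starting value is used. Serum creatinine is serial (baseline, day 1, daily on ICU, days 3 and 7; section 12.2), so its day-7 value is not an isolated reading outside that analysis. Against such a contrast the gain from adjustment is about 12, 9 and 5 points at correlations of 0.5, 0.6 and 0.7, not the full gain over the unadjusted test. But the protocol does not say that baseline enters this way, and at low correlation the contrast loses power.

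Finally, an unadjusted randomised comparison keeps its type I error, and no power was promised for secondary variables. Both points are correct.

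**Conclusion.** The point holds as a low-severity improvement and is not an error in the protocol. Section 16.1 specifies no baseline adjustment for secondary variables and leaves the role of baseline in the repeated-measures analysis open. Many safety variables and some efficacy variables have a pre-treatment value that could be used.

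Under the assumed 0.4 SD difference and 69 per arm, adjustment adds about 4 to 26 points of power over an unadjusted test across correlations of 0.3 to 0.7. Over a change or group-by-time contrast it adds about 17 to 5 points across the same range. Both inputs are assumptions; with a correlation near zero the gain vanishes. The documents do not support a claim that any stated error rate or power is missed.

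**What to change.** Add to section 16.1, or to the analysis plan before database close:

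- For each secondary variable with a pre-treatment value, compare the groups by the nonparametric analysis of covariance already cited for the primary variables, with that value as covariate. Make this the main exploratory comparison for the variable.
- State how the baseline reading enters the repeated-measures MANOVA (covariate or time level).
- Keep plain nonparametric tests for variables without a baseline, and list which variables these are.

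The cost is a few sentences and slightly more programming. No new data, visits or patients are needed.
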